# Effect of DU meridian acupuncture and temporal three-needle on vascular protection mechanisms in patients with acute cerebral infarction: a randomized controlled evaluator-blinded clinical trial

**DOI:** 10.3389/fneur.2025.1528340

**Published:** 2025-04-07

**Keywords:** acupuncture, Du meridian, acute cerebral infarction, vascular protection, protocol

## Abstract

**Background:**

The incidence of acute ischemic stroke has been rising steadily in China and globally, with its high mortality and disability rates significantly affecting quality of life. As an important adjunct therapy, acupuncture has been widely implemented in stroke management. Emerging studies have investigated the effects of DU meridian and Chong Mai acupuncture on ischemic hemiparesis; however, the vascular protective mechanisms of electroacupuncture therapy targeting these meridians require further elucidation in stroke rehabilitation research.

**Objective:**

This prospective cohort study aims to investigate the clinical efficacy and limitations of DU meridian acupuncture combined with Temporal Triple Needling (Sanjian) therapy in stroke rehabilitation. The intervention’s therapeutic potential is evaluated through its modulatory effects on CD14+/CD14- monocyte subpopulations within peripheral blood mononuclear cells (PBMCs), with particular focus on angiogenesis-mediated vascular protection mechanisms.

**Methods:**

Sixty-six patients with acute ischemic stroke will be randomly assigned 1:1 to control (conventional basal therapy, *n* = 33) and acupuncture (conventional standard stroke care + acupuncture, *n* = 33) groups for 10 days of intervention. The primary outcome is NIHSS score. The secondary outcomes: BMI and mRS scores, the level of TNF-A and IL-1B in serum, vascular endothelial growth factor (VEGF), Endocan ES, CD14+ and CD14- levels of peripheral blood mononuclear cells.

**Discussion:**

The aim of this study is to investigate whether electroacupuncture targeting the DU meridian combined with Temporal Triple Needling (Sanjian) improves cerebrovascular endothelial function in acute ischemic stroke patients, thereby reducing the NIHSS score and preventing further disease progression. This study also aims to contribute positively to the development of relevant clinical treatment protocols and to facilitate further research into the underlying mechanisms of these effects.

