### Termination criteria

Patients who meet any of the following criteria will be excluded from the study:

(1) Individuals who experience disease progression during the study that affects vital signs and requires transfer to the intensive care unit (ICU);(3) Individuals who experience serious adverse reactions or other events that impede recovery during the study;(4) Patients or family members who are unwilling to continue the clinical trial and wishing to withdraw for conciseness;(5) Individuals who exhibit intolerance to electroacupuncture or significant toxic side effects from medication during the treatment process;(6) Clinicians determine that other circumstances warrant termination of the study.

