### Outcome measurement

Clinical indicators will be conducted uniformly by professional physicians or therapists. NIHSS scores will be assessed once before treatment (Day 1), during treatment (Day 5), and after treatment (Day 10). BMI and mRS scores will be assessed before treatment (Day 1) and after treatment (Day 10).

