### Follow-up

Patients will be followed up at 1 and 3 months post-discharge, with assessments of daily living ability (using the MBI scale) and disability (using the mRS scale).

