In pain management, its mechanisms are focused on peripheral and central pathways, including reducing pain transmission and enhancing the release of endogenous opioids. In the fields of cancer pain, neurological diseases, and post-stroke recovery, acupuncture demonstrates increasing therapeutic advantages, not only improving the quality of life for patients but also offering more treatment options. However, the clinical application of acupuncture still faces many challenges, including the need for more clinical studies to further validate its efficacy and mechanisms.

The aim of this study is to determine whether acupuncture could improve vascular function in patients with AIS, thereby reducing NIHSS scores and preventing further disease progression. In this randomized controlled trial, we aim to improve patients’ neurological function and daily living abilities through acupuncture. To achieve this, we selected a series of scales and outcomes to comprehensively assess the efficacy of acupuncture. To objectively assess stroke severity, we selected the NIHSS as the primary outcome, a scale that comprehensively evaluates patients’ stroke conditions. To assess the quality of daily life, we employee the Modified Barthel Index (MBI) and the Modified Rankin Scale (mRS) as secondary outcomes.

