The trial aims to assess the efficacy of DU meridian acupuncture in treating AIS and to explore whether this acupuncture method provides vascular and brain protection by effectively inhibiting inflammation, reducing apoptosis, and promoting the generation and reconstruction of collateral circulation. These findings may offer valuable insights for the development clinical treatment options for ischemic stroke and for further investigation into the underlying mechanisms of these effects. While this study focuses on comparing acupuncture with guideline-recommended baseline treatment (antiplatelet and lipid-lowering therapy), future research could benefit from exploring other treatment strategies with potential vascular protective mechanisms. Therapies such as intensified blood pressure control, endothelial-protective agents (e.g., cilostazol), or non-pharmacological interventions (e.g., aerobic exercise) could be further investigated to deepen our understanding in future studies.

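### Preventing disease progression is a stated aim without a defined outcome, and the termination and LOCF rules can hide the patients who progress; the mechanism aims go beyond the markers measured

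*Protocol article*

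**What the plan says.** **Aims.** The abstract's Discussion sets out to learn whether the intervention improves cerebrovascular endothelial function, "thereby reducing the NIHSS score and preventing further disease progression". The main Discussion repeats this for vascular function, "thereby reducing NIHSS scores and preventing further disease progression". Its closing paragraph adds that the trial will explore whether acupuncture protects vessels and brain by "effectively inhibiting inflammation, reducing apoptosis, and promoting the generation and reconstruction of collateral circulation". The abstract's Objective names clinical efficacy, CD14+/CD14- subpopulations and angiogenesis-mediated vascular protection. It does not name progression, apoptosis or collateral circulation.

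**Outcomes.** The abstract's Methods states: "The primary outcome is NIHSS score". NIHSS is scheduled on Days 1, 5 and 10 (Outcome measurement). mRS and the Modified Barthel Index (MBI, printed as BMI in the abstract and in Outcome measurement) are taken on Days 1 and 10. For these two scales, "Patients will be followed up at 1 and 3 months post-discharge" (Follow-up). The laboratory outcomes are TNF-alpha, IL-1beta, VEGF, ES and CD14+/CD14- cells (Blood serum index).

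**Handling of progression.** Termination criterion (1) covers "Individuals who experience disease progression during the study that affects vital signs" and who need transfer to the ICU. The sentence introducing these criteria says such patients are excluded from the study. Data monitoring and statistical analysis specifies LOCF for missing values, and both an ITT and a PP analysis.

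**The concern.** The article prints both its aims and its outcomes, and the two lists do not match. Both statements of the progression aim set reducing NIHSS and preventing progression side by side as two results, yet only the first has an outcome. A difference in mean NIHSS does not say how many patients worsened: it can come from fewer patients worsening, from faster recovery among those who improve, or from both.

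The only operational use of progression is the termination rule, and that rule can remove the most informative patients from view. A favourable NIHSS result would then leave the progression aim unanswered, and the most severe progressors could be counted as unchanged. On the mechanism side, a change in blood markers cannot by itself establish less apoptosis or better collateral flow.

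**Working it through.** **1. Each aim against the outcome list**

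| Aim | Where stated | What is measured |
|---|---|---|
| Lower NIHSS | Abstract Discussion; main Discussion | NIHSS, Days 1, 5, 10 (direct) |
| Prevent progression | Abstract Discussion; main Discussion | No event, threshold or count; worsening visible in the NIHSS course and in mRS/MBI to 3 months |
| Endothelial or vascular function | Abstract Discussion; main Discussion | Circulating markers only; no functional test |
| Inhibit inflammation | Main Discussion, last paragraph | TNF-alpha, IL-1beta |
| Reduce apoptosis | Main Discussion, last paragraph | Nothing |
| Collateral circulation | Main Discussion, last paragraph | VEGF, ES, CD14 cells as indirect markers; no imaging, perfusion or vessel measure |

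**2. What the termination rule and LOCF do together**

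The article does not say whether NIHSS is still recorded after termination. If it is not:

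- ICU transfer before the Day 5 assessment: Day 5 and Day 10 both take the Day 1 score, so the recorded change is Day 1 − Day 1 = 0 and the patient counts as stable.
- ICU transfer between Day 5 and Day 10: Day 10 takes the Day 5 score, which precedes the deterioration.
- The PP set is not defined in the article, but it would probably omit both patients.
- The mRS grades printed under Secondary results run from 0 to 5, with none for death, so fatal progression has no grade there either.

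**3. What the trial is sized for**

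Inputs from Sample size: means 12.61 and 7.53 (difference 5.08), SD 5.62, u values 1.96 and 1.28, 20% dropout.

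- n = 2 × (1.96 + 1.28)² × 5.62² / 5.08² = 25.7, rounded to 26 per group.
- 26 / (1 − 0.20) = 32.5, rounded to 33 per group, 66 in total.

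The plan's figure reproduces. It rests on mean NIHSS alone.

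**4. What 33 per arm gives for a progression proportion**

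The documents give no progression rate. The control rates p₁ below are assumptions, with treatment assumed to halve them (p₂ = p₁/2). With p̄ the average of the two rates:

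- SE₀ = √(2p̄(1 − p̄)/33) and SE₁ = √((p₁(1 − p₁) + p₂(1 − p₂))/33)
- Power = Φ((p₁ − p₂ − 1.96 × SE₀)/SE₁)
- Approximate 95% CI half-width for the difference = 1.96 × SE₁

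For 20% against 10%: SE₀ = 0.0879 and SE₁ = 0.0870, so (0.10 − 0.1723)/0.0870 = −0.83. Power is 0.203 and the half-width 0.171.

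| Assumed rates | Power, 33 per arm | CI half-width | Per arm for 90% power |
|---|---|---|---|
| 10% v 5% | 12% | ±12.7 points | 582 |
| 20% v 10% | 20% | ±17.1 points | 266 |
| 30% v 15% | 31% | ±19.8 points | 161 |

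A progression outcome at this size can describe but not confirm. The scheduled data for it exist: 66 patients × 3 assessments = 198 planned NIHSS scores.

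**The case against.** A sponsor could fairly answer as follows.

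- **Worsening is measured.** NIHSS is a serial deficit score on which higher is worse, and mRS and MBI run to 3 months. This stands. A reader might infer that the trial collects nothing on progression and cannot address it at all, and the documents do not support that. What is missing is a definition, together with protection of the progressors' data.
- **A threshold can be left to the full protocol or SAP.** True of the threshold. But the article lists its outcomes, and progression is not among them although it is twice stated as an aim. No later document can supply apoptosis data that are not collected.
- **Apoptosis and collaterals are exploratory.** This stands: they appear as trial aims only in the closing Discussion paragraph, as something to explore, and not in the Objective.
- **The mechanism is not without data.** This stands for collaterals. The main Discussion links VEGF, ES and CD14 cells to angiogenesis and openly calls the markers serological indicators of vascular health. They remain indirect.
- **The termination rule is narrow.** This stands: it acts after randomisation and covers only progression that needs ICU care. It is not an entry exclusion, though the text does use the word excluded.

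A reader might also infer that a lower mean NIHSS here would come only from patients who were improving anyway, or that the results will be reported as prevented progression. The documents give no recovery rates and set no such reporting rule, so neither can be claimed.

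**Conclusion.** The point holds in limited form. Prevention of progression, stated twice as an aim, has no defined outcome. The termination rule with LOCF can score the most severe progressors at values from before they deteriorated; this rests on the assumption that NIHSS is not recorded after termination, which the article leaves open. Apoptosis is not measured. Collateral circulation and endothelial function are addressed only through circulating markers.

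The size of any distortion cannot be calculated, because the documents give no rate of progression or ICU transfer. The 12% to 31% power range depends wholly on the assumed control rates and the assumed halving. It shows only that a progression outcome must be exploratory. The choice of primary outcome and the sample size of 66 are unaffected. The change is worth making because it is cheap and keeps the conclusions within what is measured.

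**What to change.** 1. **Add an exploratory secondary outcome, progression by Day 10**, counted in all randomised patients, including those terminated. Define it as a rise in total NIHSS from Day 1 to Day 5 or Day 10 by at least a threshold fixed before unblinding, or ICU transfer for neurological worsening, or death. Report the proportion per arm and the difference with a confidence interval.
2. **Keep recording NIHSS and vital status after treatment is terminated**, as far as consent allows, and say so under Termination criteria. ICU transfer and death then count as events and are not replaced by a carried-forward score.
3. **Narrow the mechanism aims** in the abstract's Discussion and the main Discussion to changes in circulating inflammatory and angiogenic markers. Remove apoptosis. Describe collateral circulation and endothelial or vascular function as hypotheses that the trial does not directly test.

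**Cost:** protocol wording, one derived variable, and continued recording for terminated patients. The last may be new work, since the article does not show that it is already planned. No new laboratory test and no change to sample size or treatment is needed. The downsides are an imprecise progression estimate with 33 per arm and a narrower mechanistic claim.

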**Clinical trial registration:**

International Traditional Medicine Clinical Trial Registry ITMCTR2024000508.

## Introduction

Stroke is currently recognized as the second leading cause of disability and mortality worldwide (1), with acute ischemic stroke accounting for approximately 85% of cases (2). In China, the incidence of stroke has been increasing annually over the past 30 years, making it the leading cause of death in the country (3). Stroke is characterized by high incidence rates, high recurrence rates, high disability rates, and high case fatality rates (4). Acute ischemic stroke (AIS) refers to a group of syndromes caused by various factors leading to impaired blood supply to brain tissue (5). This impairment triggers a series of cascade reactions, resulting in ischemic and hypoxic necrosis in the brain, as well as neurological deficits in clinical practice (6). The current preferred treatment methods include intravenous thrombolysis and intravascular intervention therapy (7). However, treatment for AIS is often delayed due to factors such as low public awareness, a narrow thrombolysis time window, and strict eligibility criteria for thrombolysis. Only 21.5% of AIS patients in China arrive at the emergency department within 3 h of onset, and 12.6% are eligible for thrombolysis treatment, with fewer than 3% actually receiving it. The average interval between patient arrival at the emergency department and the administration of thrombolytic drugs is 116 min, significantly longer than in developed countries (8). Very few patients in China receive timely and effective thrombolytic therapy within the designated time window; therefore, it is essential for these patients to seek alternative treatments. Acute cerebral infarction is classified as a type of “stroke” in traditional Chinese medicine. Acupuncture, an important adjunctive treatment during the acute phase of cerebral infarction (9), has been shown to promote collateral circulation and improve brain circulation and metabolism to some extent (10). Currently, some scholars recommend initiating acupuncture treatment as soon as the patient’s vital signs stabilize (11). Therefore, in the early stages of acute ischemic stroke, when thrombolysis is no longer feasible and medical conditions are underdeveloped, acupuncture may offer timely intervention to mitigate the extent of cerebral infarction, reduce sequelae, and decrease the likelihood of functional disability, thereby conserving social resources (12).

## Materials and methods

### Participants

Emergency inpatients admitted to the First Affiliated Hospital of Guangzhou University of Chinese Medicine, who meet the diagnostic criteria for acute cerebral infarction as outlined in the “Guidelines for the Prevention and Treatment of Stroke in China” (2021 edition) (13), and who provide informed consent, will be included.

### Study design

This is a randomized controlled trial with evaluator blinding to be conducted at the First Affiliated Hospital of Guangzhou University of Chinese Medicine. A total of 66 emergency inpatients will participate in this study. The experimental flowchart is shown in Figure 1. This study has received approval from the Ethics Committee of the First Affiliated Hospital of Guangzhou University of Traditional Chinese Medicine (Ethics Acceptance Number: JY2024-116).

**Figure 1 fig1:**
[figure not shown]
Flow chat of the study.

### Diagnostic criteria

(1) Diagnostic criteria: The diagnostic criteria for acute cerebral infarction will refer to the “Guidelines for the Prevention and Treatment of Stroke in China” (2021 edition) formulated by the Neurology Branch of the Chinese Medical Association (9).(2) Traditional Chinese Medicine (TCM) Diagnosis criteria: The diagnostic criteria for disease classifications are based on the “Diagnosis and Efficacy Evaluation Criteria for Stroke (Trial)” developed by the National Research Collaboration Group on Traditional Chinese Medicine Brain Disease Emergencies under the State Administration of Traditional Chinese Medicine.

### Inclusion criteria

(1) Meets the diagnostic criteria for acute cerebral infarction as outlined in the “Guidelines for the Prevention and Treatment of Stroke in China” (2021 edition), and diagnosed through head CT or MRI examination;(2) Meets the diagnostic criteria for stroke as defined by Traditional Chinese Medicine (TCM);(3) Individuals experiencing their first stroke within 7 days of onset and are aged between 35 and 75 years;(4) NIHSS score ≥ 3 and ≤ 20, with no physical disability related to the study prior to disease onset;(5) Clear consciousness, defined as GCS score ≥ 13 points;(6) Individuals who voluntarily participate in this study and provide informed consent form.

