### Random allocation

A total of 66 patients were enrolled using simple randomization with a random number table and randomly assigned to the treatment group and the control group. The group assignments and treatment protocols were placed in opaque envelopes and kept by the attending physicians and acupuncture therapists, who administered the treatment according to the instructions in the envelopes.

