### Blood serum index

In this study, enzyme-linked immunosorbent assay (ELISA) will quantify patients’ expression of inflammatory factors, including TNF-*α* and IL-1β (25), vascular endothelial growth factor (VEGF) (26), endothelial repressor ES (27),and peripheral blood mononuclear cells at pre-trial (Day 1), on-treatment (Day 5), and post-treatment (Day 10) levels. Additionally, flow cytometry will measure the CD14+ and CD14- levels of mononuclear cells in peripheral blood (28).

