Acupuncture improves blood and oxygen supply to the ischemic hemiparesis (33), effectively protects cerebral blood vessels, and restores brain function (34). Acupuncture has been widely used to treat stroke sequelae; however, its therapeutic effects and specific vascular protection mechanisms during the acute stage of stroke remain poorly understand. Existing studies suggest that potential vascular protection mechanisms can be categorized as follows: first, the effects of pro-angiogenic factors, including the regulation of VEGF/VEGFR (35), angiopoietin and its receptor Ang/Tie, basic fibroblast growth factor (bFGF), Apelin/APJ in vascular endothelial cells, and the expression of endothelial progenitor cells (EPCs) as well as the regulation of the Wnt/*β*-catenin signaling pathway; second, the effects of inhibitory angiogenesis factors, primarily characterized by reduction of endostatin (ES) expression (36). Intervention with endothelial progenitor cells (EPCs) using “acupuncture serum” collected from acupuncture points resulted in a significant increase in the proliferation, migration, and adhesion of these EPCs (37), indicating that acupuncture promotes angiogenesis following cerebral ischemia. EPCs can be derived from the CD14+ and CD14-cell subsets of adult peripheral blood mononuclear cells. Both subsets can express marker proteins and differentiate into endothelial cells under the stimulation of growth factors, thus promoting neovascularization. However, it remains unclear whether acupuncture can effectively increase the expression levels of CD14+ and CD14- cells in peripheral blood mononuclear cells, leading to the formation of EPCs. This study aims to determine whether acupuncture can promote blood vessel regeneration by increasing the expression of these CD14+ and CD14- cells, thereby enhancing vascular protection.

During the acute phase of cerebral infarction, blood–brain barrier damage and endothelial cell degeneration occur in patients with acute ischemic stroke (AIS), accompanied by elevated levels of TNF-*α* and IL-1β (37). To elucidate the vasoprotective mechanism of DU meridian acupuncture, the levels of inflammatory factors TNF-α and IL-1βas well as vascular endothelial growth factor (VEGF), endothelial repressor (ES) expression, and CD14+ and CD14- cell levels in peripheral blood mononuclear cells (28). These serve as serological indicators for assessing improvements in vascular health.

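### Time since stroke onset, anywhere from 0 to 7 days at entry, is not balanced by design and enters no stated comparison; adding it as a covariate is a minor gain in precision

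*Protocol article*

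**What the plan says.** All references are to the protocol article.

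- **Inclusion criteria, item (3):** entry is open to "Individuals experiencing their first stroke within 7 days of onset". This is the only use the document makes of time since onset.
- **Outcome measurement:** "NIHSS scores will be assessed once before treatment (Day 1), during treatment (Day 5), and after treatment (Day 10"). Day 1 is defined by the start of treatment, not by the stroke.
- **Blood serum index:** the markers follow the same clock, "peripheral blood mononuclear cells at pre-trial (Day 1), on-treatment (Day 5), and post-treatment (Day 10) levels".
- **Random allocation:** the 66 patients are allocated by "simple randomization with a random number table". No stratification or minimisation factor is given.
- **Data monitoring and statistical analysis:** for normally distributed data the section lists the t-test, repeated-measures ANOVA and multivariate linear regression. It names no covariate for any of them.
- **Discussion:** the acute phase of infarction is described as "accompanied by elevated levels of TNF"-α and IL-1β, so at least these two markers are linked to the stage of disease.

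**The concern.** Two patients at the same trial visit may be a week apart in the course of their stroke. A late entrant's baseline sample can be taken later after onset than an early entrant's on-treatment sample. If NIHSS or the markers change with time since onset, this spread adds variance to every comparison. A chance difference between arms in mean onset time would also pass into the estimated treatment effect. With 66 patients and unrestricted allocation, nothing in the design limits that difference. The interval must already be known for each patient in order to apply item (3), so an available prognostic variable may go unused.

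**Working it through.** **1. The plan's own figure.** Inputs from the Sample size section: means 7.53 and 12.61 (difference 5.08), SD 5.62, two-sided α = 0.05, power 90%.

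n = 2 × (1.96 + 1.28)² × 5.62² / 5.08² = 25.70, so 26 per arm. Then 26 / (1 − 0.20) = 32.5, so 33 per arm and 66 in total. This reproduces.

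**2. Visits on the onset clock.** Day 5 is 4 days after Day 1, and Day 10 is 9 days after it.

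| Trial visit | Days since onset |
|---|---|
| Day 1 | 0-7 |
| Day 5 | 4-11 |
| Day 10 | 9-16 |

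Day 1 overlaps Day 5, and Day 5 overlaps Day 10.

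**3. Chance imbalance between arms.** The document gives no distribution of entry times. *Assumption:* uniform over 0-7 days, so SD = 7/√12 = 2.02 days. The expected difference in mean onset time between arms is 0, with SE = 2.02 × √(2/n).

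- n = 33: SE = 0.50 day, 95% range ±0.98 day.
- n = 26: SE = 0.56 day, 95% range ±1.10 days.

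Simulating simple randomisation of 66 patients gives the same 95% limit (0.98 day). A difference above 1 day occurs in about 4.5% of allocations.

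To show how far this depends on the assumption:

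- Entry uniform over only the first half of the window: SD = 3.5/√12 = 1.01, range ±1.96 × 1.01 × √(2/33) = ±0.49 day.
- The largest SD the window allows (half the patients at 0 days, half at 7): SD = 3.5, range ±1.96 × 3.5 × √(2/33) = ±1.69 days.

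**4. On the NIHSS scale.** The document gives no slope of NIHSS on time since onset. *Assumption:* 0.25, 0.5 or 1.0 points per day. The 95% chance shift is slope × 0.975 day (33 per arm, uniform entry over 0-7 days).

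| Slope | Chance shift | Share of 5.08 |
|---|---|---|
| 0.25 | 0.24 points | 5% |
| 0.5 | 0.49 points | 10% |
| 1.0 | 0.98 points | 19% |

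**5. Type I error.** With outcome SD 5.62 plus slope × onset time, 33 per arm and no true effect, the unadjusted t-test rejected in 4.9-5.2% of 20,000 simulated trials at each of the three slopes. It is intact.

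**6. Power.** There are two possible readings of the planning SD.

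- *Onset variation comes on top of 5.62.* SD = √(5.62² + (slope × 2.02)²) = 5.64, 5.71 or 5.97. Power at 26 per arm goes from 90.3% to 90.1%, 89.4% or 86.6%. The number per arm for 90% power is 26, 27 or 30.
- *5.62 already contains it.* Planned power is unchanged. Adjustment would reduce the number needed per arm from 26 to 26, 25 or 23.

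**7. Markers.** The document gives neither an SD nor a slope for any marker, so no corresponding figure can be derived.

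**The case against.** A reader might infer that the arms are compared at different stages of disease, so that the treatment effect is biased. The document does not support that. Both arms have the same entry window and are randomised 1:1, so the mix of onset times is equal in expectation. The overlap in step 2 is between patients, not between arms. Counting visits from the start of a fixed 10-day treatment is ordinary practice.

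A reader might also infer that the plan has no control for onset time at all. That is not established. Multivariate linear regression is planned, its covariates are not listed, and such a list is commonly left to an analysis plan, which is not shown here. What the article does fix is the 7-day window, the Day 1 clock and simple randomisation. Simple randomisation is a valid method.

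It is tempting to add that early entrants have more spontaneous change ahead of them. No section says so. The Introduction speaks of a cascade without giving its timing. The Discussion ties TNF-α and IL-1β to the acute phase without describing how they change within the first week, and it gives no time course for VEGF or the cell counts.

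Finally, days of imbalance can sound larger than they are. Under uniform entry, a difference above half a day has a 31-37% chance (33 and 26 per arm). At the assumed slopes, half a day is worth only 0.125-0.5 NIHSS points. All of these objections stand. They limit the point to precision, but they do not remove the benefit of using a variable already in hand.

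**Conclusion.** The point holds as a minor improvement in precision. Time since onset varies by up to 7 days at every visit, is not balanced by design, and is not said to enter any comparison. The consequence is noise and chance imbalance, not systematic bias or an inflated type I error. The sample size stands.

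The size in steps 3 and 4 rests on two assumptions that the document cannot confirm: the spread of entry times and the NIHSS slope per day. Even at the steepest assumed slope, the 95% chance shift under uniform entry is below one NIHSS point. The planned difference used as the yardstick comes from a comparison after 2 weeks of treatment, whereas the last NIHSS here is at Day 10. Any relevance to the markers is plausible from the Discussion but cannot be quantified.

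**What to change.** Keep the 7-day window. State that the between-group comparison of Day 10 NIHSS, and of each blood marker, is a linear model (ANCOVA) with treatment group, the baseline value of that outcome and the onset-to-Day 1 interval as pre-specified covariates. This replaces the unadjusted t-test and falls within the regression already listed under Data monitoring and statistical analysis. Naming the covariates in advance also avoids a post hoc decision if an imbalance appears.

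The cost is a sentence of analysis text and recording the interval as a number of days. No visits or patients are added.

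Two further steps are optional. Allocation could be stratified by early versus late entry with a pre-set cut, but only if enrolment has not begun. Markers could also be displayed by days since onset, although 66 patients spread over about 0-16 days would make this descriptive only.
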